## Methods

### Study design

Pragmatic cluster randomized controlled trial with additional qualitative and quantitative process evaluations. The CONSORT statement on pragmatic trials was used to assist with the design
[21].

### Target population

Patients with Type 2 Diabetes attending 45 Community Health Centres in the Cape Town Metropole were the target population. Thirty eight health promoters are currently employed within these facilities.

### Sample size

Data from a previous study in the same population (n=450, 18 clinics) showed that the mean HbA1c was 8.8% (SD 3.3) and intraclass correlation 0.1
[22]. Similarly the mean weight was 78.2Kg (SD 16.7) and intraclass correlation 0.05. These figures were used to calculate the sample and cluster size for a 5% weight reduction and a 1% reduction in HbA1c. Based on a level of significance of 0.05 and a power of 0.8 the study required 17 clusters in each arm with 40 patients per cluster. The total sample size therefore would be 34 clusters (health centres) and 1360 patients.

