[7]. A systematic review of group education in diabetes concluded that “The results of the meta-analyses in favour of group-based diabetes education programmes were: reduced glycated haemoglobin at four to six months (1.4%; 95% confidence interval (CI) 0.8 to 1.9; P < 0.00001), at 12–14 months (0.8%; 95% CI 0.7 to 1.0; P < 0.00001) and two years (1.0%; 95% CI 0.5 to 1.4; P< 0.00001); reduced fasting blood glucose levels at 12 months (1.2 mmol/L; 95% CI 0.7 to 1.6; P < 0.00001); reduced body weight at 12–14 months (1.6 Kg; 95% CI 0.3 to 3.0; P = 0.02); improved diabetes knowledge at 12–14 months (SMD 1.0; 95% CI 0.7 to1.2; P < 0.00001) and reduced systolic blood pressure at four to six months (5 mmHg: 95% CI 1 to 10; P = 0.01). There was also a reduced need for diabetes medication (odds ratio 11.8, 95% CI 5.2 to 26.9; P < 0.00001; RD = 0.2; NNT = 5). Therefore, for every five patients attending a group-based education programme we could expect one patient to reduce diabetes medication”
[17]. Motivational interviewing in group format is a relatively new development; 12 published reports have emerged
[18,19], which include three randomized trials and one study in the diabetes field
[20].

Despite evidence of the effectiveness of group diabetes education all of the trials have been conducted in high-income countries and by health professionals such as doctors or nurses. This trial will be the first in an African context and delivered by mid-level health workers. In addition the incorporation of group motivational interviewing will add to a small evidence base on this topic.

If the study demonstrates effectiveness of this educational intervention then it can be implemented throughout the Western Cape and may well be replicated in the rest of the country and possibly within the southern African Region. The study intends to inform policy makers and managers of the district health services and help them decide whether to implement the programme more widely.

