### Aim and objectives

Aim: To evaluate, by means of a pragmatic cluster randomized controlled trial, the effectiveness of a group diabetes education programme delivered by trained health promoters with a guiding (motivational interviewing) style, in community health centres in Cape Town, South Africa.

Objective 1: To evaluate effectiveness by assessing group changes in the following:

*Primary outcomes:* improved diabetes self-care activities, 5% weight loss, HbA1c reduction of 1 percentage point

*Secondary outcomes:* improved diabetes-specific self-efficacy, locus of control, mean blood pressure, mean weight loss, mean waist circumference, mean HbA1c, mean total cholesterol and quality of life

Objective 2: To evaluate fidelity to the educational programme and motivational interviewing by use of audiotapes and scoring health promoters with the Motivational Interviewing Integrity Code.

Objective 3: To explore the experiences of the health promoters with regards to their training and delivery of the diabetes education programme.

Objective 4: To explore the experiences of patients who attend the diabetes education sessions.

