### Data analysis

Intention-to-treat analysis will evaluate the primary and secondary outcomes. Any missing baseline data will be imputed using the Markov chain Monte Carlo approach. Missing status at follow-up will be modelled on baseline covariates and randomised group using logistic regression. Inverse probability weighting will be used for the final trial analysis. Models for comparing continuous outcomes will use linear regression and for categorical outcomes will use logistic regression with adjustment for baseline covariates and clustering.

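### The stated 80% power does not apply to the primary weight outcome: the calculation compares mean body weights between arms, but the outcome is 5% weight loss within patients

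*Protocol article*

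**What the plan says.** All references are to the protocol article. The Sample size section draws on an earlier study of 450 patients in 18 clinics. For weight it reports: "Similarly the mean weight was 78.2Kg (SD 16.7) and intraclass correlation 0.05". It then says: "These figures were used to calculate the sample and cluster size for a 5% weight reduction and a 1% reduction in HbA1c". The design criteria are "Based on a level of significance of 0.05 and a power of 0.8", which leaves the sidedness open, and the result is 17 centres of 40 patients in each arm, 1360 patients in all. The abstract repeats this total and attaches 80% power to the primary outcomes.

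Aim and objectives lists the primary outcomes as "improved diabetes self-care activities, 5% weight loss, HbA1c reduction of 1 percentage point". The secondary list contains "mean blood pressure, mean weight loss, mean waist circumference" among others. Mean body weight as such is not an outcome. The Data collection process section has each patient measured at baseline and again at 12 months. The Data analysis section uses linear regression for continuous outcomes and, for categorical ones, "logistic regression with adjustment for baseline covariates and clustering".

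**The concern.** An SD of 16.7 kg around a mean of 78.2 kg describes how much patients differ from one another when weighed once. Much of that spread is stable and cancels when each patient is compared with his or her own baseline. Neither the SD nor the intraclass correlation (ICC) of a weight level can be assumed to hold for a weight change. Neither gives the power for a proportion, which depends on the control rate, the difference in rates and the ICC of the binary outcome.

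The article lists 5% weight loss and mean weight loss as separate outcomes and assigns categorical outcomes to logistic regression. The primary weight outcome therefore reads most naturally as a responder proportion, and the inputs shown give no power for it. The result is meant to inform a decision on wider roll-out. A reader who relies on the 80% to interpret a null or positive weight result would be relying on a figure for a different quantity.

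**Working it through.** **Inputs from the Sample size section.** Weight: mean 78.2 kg, SD 16.7, ICC 0.05. HbA1c: "showed that the mean HbA1c was 8.8% (SD 3.3) and intraclass correlation 0.1", difference 1 point. Alpha 0.05, power 0.80, m = 40 per centre, k = 17 centres per arm (680 patients per arm).

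**1. Reproducing the 17 centres.** The weight difference is 0.05 × 78.2 = 3.91 kg. The design effect is 1 + 39 × 0.05 = 2.95. Centres per arm = 2 × [SD × (z_alpha + z_power) / difference]² × design effect / 40.
- One-sided 0.05: 2 × [16.7 × (1.645 + 0.842) / 3.91]² = 225.6; × 2.95 = 665; / 40 = 16.6, so 17.
- Two-sided 0.05: 2 × [16.7 × (1.960 + 0.842) / 3.91]² = 286.4; × 2.95 = 845; / 40 = 21.1, so 22.

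HbA1c behaves the same way (design effect 4.9): 16.5 centres one-sided, so 17, and 20.9 two-sided, so 21. The stated 17 is recovered for both outcomes as an unadjusted comparison of mean levels with a one-sided 0.05 test.

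**2. Power on the plan's own weight inputs.** SE = 16.7 × √(2 × 2.95 / 680) = 1.56 kg. At 3.91 kg, power is 0.81 one-sided and 0.71 two-sided. At 1.6 kg, the effect in the review cited in Background ("reduced body weight at 12–14 months (1.6 Kg; 95% CI 0.3 to 3.0; P = 0.02"), it is 0.18 two-sided.

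**3. Mean weight loss (secondary).** The article gives no baseline to 12-month correlation r, so r is an assumption here. SD of change = 16.7 × √(2(1 − r)), which equals 16.7 at r = 0.5 and is smaller above that. With the ICC kept at 0.05 and a two-sided test at 17 × 40:

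| r (assumed) | SD of change, kg | SE, kg | Power at 1.6 kg | Centres per arm for 3.91 kg |
|---|---|---|---|---|
| 0.50 | 16.7 | 1.56 | 0.18 | 21.1 |
| 0.80 | 10.6 | 0.98 | 0.37 | 8.5 |
| 0.90 | 7.5 | 0.70 | 0.63 | 4.2 |
| 0.95 | 5.3 | 0.49 | 0.90 | 2.1 |
| 0.97 | 4.1 | 0.38 | 0.99 | 1.3 |

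The ICC of change is also unknown. At ICC 0.10 with baseline adjustment (residual SD 16.7 × √(1 − r²)), power at 1.6 kg is about 0.45 at r = 0.90 and 0.91 at r = 0.97.

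**4. Proportion losing 5% (primary, on the natural reading).** The article gives no rates, so these scenarios are also assumptions. Two-sided 0.05, normal approximation with a pooled null variance, effective size per arm 680 / design effect:

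| Control v intervention | ICC | Centres per arm for 80% | Power at 17 × 40 |
|---|---|---|---|
| 5% v 10% | 0.05 | 32.1 | 0.53 |
| 5% v 10% | 0.01 | 15.1 | 0.85 |
| 10% v 15% | 0.05 | 50.6 | 0.37 |
| 10% v 15% | 0.01 | 23.8 | 0.66 |
| 10% v 20% | 0.05 | 14.7 | 0.86 |
| 10% v 20% | 0.01 | 6.9 | 0.99 |
| 20% v 30% | 0.05 | 21.7 | 0.70 |

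Power falls on either side of 0.80 depending on the scenario. The table is illustrative and not a bound: 20% v 25% at ICC 0.05 gives 0.25.

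**The case against.** The strongest reply is that an SD of a level is a familiar conservative stand-in when no SD of change is available. For mean weight loss that is fair: at an unchanged ICC the inputs overstate the variance whenever r exceeds 0.5, and with baseline adjustment whenever r is not zero. HbA1c leads to 17 centres by the same route, so correcting weight alone would not change the size of the trial. Recruitment and follow-up are complete. Choosing 3.91 kg as a target is also legitimate, although it lies above the upper confidence limit of 3.0 kg in the cited review. And an article condenses, so a fuller calculation may exist elsewhere.

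These points stand, but none supplies a power for the primary weight outcome. The article names the inputs it used, and they reproduce its answer as a comparison of mean weights. Conservatism for a mean does not carry over to a proportion. Nor does the larger recruitment (720 and 850) restore 80% two-sided. Spread evenly over 17 centres per arm, SE = 16.7 × √(3.07/720 + 3.45/850) = 1.52 kg, so power at 3.91 kg is about 0.73 before any loss to follow-up.

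Three stronger readings are tempting and not supported. A reader might infer that the trial can resolve weight effects of 1 to 2 kg, so that a null weight result could not be put down to low power. That concerns only the secondary mean and rests on a high r that the article does not give; at r = 0.80, power at 1.6 kg is 0.37. A reader might infer that the trial has more centres than weight needs; several responder scenarios need more than 17. A reader might infer that HbA1c limits the design. But its SD of 3.3 is cross-sectional too, and 5% v 10% or 10% v 15% at ICC 0.05 would need 32 or 51 centres per arm, against 21 for HbA1c.

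**Conclusion.** The point holds in a limited form. The weight calculation describes a 3.91 kg difference in mean body weight, which is not an outcome of this trial, so the abstract's 80% is not the power for 5% weight loss. On its own inputs the figure is 81% one-sided and 71% two-sided. The documents do not say which test was intended; one-sided is inferred from the reproduction.

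For mean weight loss the stated inputs are probably pessimistic: SE 0.98 to 0.38 kg against 1.56 kg, and power at 1.6 kg of 37% to 99% against 18%, assuming r of 0.80 to 0.97 and ICC 0.05. For the responder outcome neither the size nor the direction of the error can be settled from the documents; power runs from 0.37 to 0.99 over the scenarios tabulated. If the primary outcome were instead a mean percentage change, it would still be a within-patient change and 16.7 kg would still not be its SD. The design is not invalidated. The stated power for weight should be corrected.

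**What to change.** Leave recruitment as it is and restate the power in the Sample size section and the abstract, giving the sidedness of the test.

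- For the primary weight outcome, say that it is the proportion of patients losing 5%, if that is what is meant. Give power for it over stated control rates, differences and ICCs.
- For mean weight loss, give power or the expected confidence-interval half-width from the SD and ICC of 12-month change, or of baseline-adjusted follow-up weight. Take these from the trial's pooled data without arm labels and say so, or show a stated range. Report the result at the cited 1.6 kg as well as at 3.91 kg.
- Note that the HbA1c SD of 3.3 is likewise cross-sectional, and do not name HbA1c as the outcome that limits the design.

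The cost is one paragraph and a short recalculation. The stated power may come out less favourable than 80%.

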**Methods:**

**Trial design:** Pragmatic cluster randomized controlled trial

**Participants:** Type 2 diabetic patients attending 45 public sector community health centres in Cape Town

**Interventions:** The intervention group will receive 4 sessions of group diabetes education delivered by a health promotion officer in a guiding style. The control group will receive usual care which consists of ad hoc advice during consultations and occasional educational talks in the waiting room.

**Objective:** To evaluate the effectiveness of the group diabetes education programme

**Outcomes:** Primary outcomes: diabetes self-care activities, 5% weight loss, 1% reduction in HbA1c. Secondary outcomes: self-efficacy, locus of control, mean blood pressure, mean weight loss, mean waist circumference, mean HbA1c, mean total cholesterol, quality of life

**Randomisation:** Computer generated random numbers

**Blinding:** Patients, health promoters and research assistants could not be blinded to the health centre’s allocation

**Numbers randomized:** Seventeen health centres (34 in total) will be randomly assigned to either control or intervention groups. A sample size of 1360 patients in 34 clusters of 40 patients will give a power of 80% to detect the primary outcomes with 5% precision. Altogether 720 patients were recruited in the intervention arm and 850 in the control arm giving a total of 1570.

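### With the article's own inputs, 17 centres per arm of 40 patients give about 71% power in an unadjusted two-sided 5% test; the stated 80% rests on an assumption that the article does not declare.

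*Protocol article*

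**What the plan says.** The Sample size section takes its inputs from an earlier study in the same population: "the mean HbA1c was 8.8% (SD 3.3) and intraclass correlation 0.1", and "the mean weight was 78.2Kg (SD 16.7) and intraclass correlation 0.05". The targets are a 5% weight reduction and a 1% HbA1c reduction; Aim and objectives makes clear that the latter is one percentage point. The section sets the significance level at 0.05 and concludes that, for "a power of 0.8 the study required 17 clusters in each arm with 40 patients per cluster". It mentions no sidedness, no baseline-to-follow-up correlation and no gain from covariate adjustment.

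The abstract (Methods, Numbers randomized) says: "A sample size of 1360 patients in 34 clusters of 40 patients will give a power of 80% to detect the primary outcomes". It lists three primary outcomes: self-care activities, 5% weight loss and a 1% HbA1c reduction.

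The Data analysis section plans linear and logistic regression adjusted for baseline covariates and clustering. It does not say whether tests are one-sided or two-sided.

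**The concern.** A 0.05 level given without qualification is normally read as two-sided. On that reading the inputs do not lead to 17 centres per arm, and the design falls roughly nine percentage points short of the stated power.

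The trial is meant to inform a decision on wider implementation. Readers of a non-significant result would credit the trial with 80% power to detect the stated differences, which an unadjusted two-sided test does not have.

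The abstract also extends the 80% to all primary outcomes, although the Sample size section calculates only for weight and HbA1c.

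**Working it through.** **Inputs (Sample size section).**
- HbA1c: SD 3.3, intraclass correlation (ICC) 0.1, difference 1.0 point.
- Weight: SD 16.7 kg, ICC 0.05, difference 5% of 78.2 = 3.91 kg.
- 40 patients per centre, 17 centres per arm (680 patients per arm), level 0.05, power 0.8.

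Because the section supplies means and SDs, I take the calculation to be a comparison of two means.

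**Formulas.** Design effect DE = 1 + (40 − 1) × ICC, which is 4.9 for HbA1c and 2.95 for weight. Centres per arm = 2 (z_α + z_β)² SD² / difference² × DE / 40, with z_β = 0.842.

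**Reproducing the stated 17 (one-sided, z_α = 1.645).**
- HbA1c: 134.7 × 4.9 = 659.8 patients; /40 = 16.5, rounded up to 17.
- Weight: 225.6 × 2.95 = 665.4 patients; /40 = 16.6, rounded up to 17.

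Both outcomes return the article's figure.

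**The same calculation, two-sided (z_α = 1.960).**
- HbA1c: 170.9 × 4.9 = 837.6 patients; /40 = 20.9, rounded up to 21.
- Weight: 286.4 × 2.95 = 844.8 patients; /40 = 21.1, rounded up to 22.

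With a t test on 2 × 17 − 2 = 32 degrees of freedom for the power at 17 centres, and the matching degrees of freedom for the number needed, the requirements become 22 and 23.

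**Power at 17 × 40 per arm.** SE = SD × √(2 × DE / 680).
- HbA1c: SE = 3.3 × √(2 × 4.9 / 680) = 0.396; 1/0.396 = 2.524; power = Φ(2.524 − 1.960) = 71.4%.
- Weight: SE = 16.7 × √(2 × 2.95 / 680) = 1.556; 3.91/1.556 = 2.514; power = Φ(2.514 − 1.960) = 71.0%.

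| Test at 5% | HbA1c | Weight |
|---|---|---|
| One-sided, normal | 81.0% | 80.8% |
| One-sided, t on 32 df | 79.5% | 79.3% |
| Two-sided, normal | 71.4% | 71.0% |
| Two-sided, t on 32 df | 68.7% | 68.4% |

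The difference detectable with 80% two-sided power is (1.960 + 0.842) × SE: 2.802 × 0.396 = 1.11 points and 2.802 × 1.556 = 4.36 kg.

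**Other routes to 17.**
- *Baseline adjustment.* Assume that adjustment multiplies the variance by 1 − r² at both the patient and the centre level. Two-sided, 20.94 × (1 − r²) rounds up to 17 for r of about 0.434 to 0.486 (HbA1c), and 21.12 × (1 − r²) does so for about 0.442 to 0.492 (weight). A common r of roughly 0.44 to 0.48 therefore gives 17 for both (normal approximation).
- *ICC misread as a between-centre coefficient of variation.* Two-sided, this gives 16.1, so 17, for HbA1c but 23.1, so 24, for weight. It does not explain both.

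**Numbers actually recruited.** The 720 and 850 patients reported under Sample selection process, assumed to be spread evenly over 17 centres per arm, give two-sided power of 72.4% and 72.8% (normal). The extra patients do not close the gap.

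**The case against.** The strongest reply is that the article never says two-sided. Its inputs do give 17 centres and about 81% power with a one-sided 5% test, so a reader who infers that the 80% is simply an arithmetical error goes too far. A condensed article may also leave sidedness to the full protocol. This stands: the defect is an undeclared assumption behind a headline figure, and the shortfall exists on the two-sided reading.

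A second reply is that 71% is not the power of the planned analysis. Data analysis specifies adjustment for baseline covariates, and HbA1c and weight are measured at baseline and at 12 months. Adjustment could bring two-sided power to 80% with a correlation of about 0.44. This also stands, so 71% must be labelled as unadjusted. For the same reason a reader should not infer that a one-sided test is the sole route to 17. But the Sample size section states no correlation and claims no gain from adjustment, so the reply cannot support the 80% as written.

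A reader might further infer that the trial will test at one-sided 5% and so double the usual false-positive allowance in the favourable direction. The documents do not support that. A one-sided quantile in a planning formula says nothing about how outcomes will be tested, and Data analysis is silent on it.

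Finally, Aim and objectives lists mean HbA1c and mean weight loss as secondary outcomes, while the primary ones can be read as thresholds reached by individual patients. The figures here concern mean differences, so any restated power must say so.

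**Conclusion.** The concern holds in this form. On the conventional two-sided reading of 0.05, and without baseline adjustment, 17 centres per arm of 40 have about 71% power (68–69% with 32 degrees of freedom) for the stated differences, and 80% would need 21 to 22 centres per arm by the normal approximation. An undeclared one-sided level is the likely source, because two outcomes with different SDs, ICCs and differences both land on 17. It remains an inference.

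The result rests on equal centres of 40, the quoted SDs and ICCs, and a comparison of means. Whether the adjusted analysis reaches 80% depends on a correlation that the article does not give.

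The abstract's claim for the primary outcomes as a group is unsupported whatever the sidedness, because self-care activities have no calculation.

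**What to change.** Change the wording in the abstract and the Sample size section; no further enrolment is needed.

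1. Declare whether the 0.05 level is one-sided or two-sided.
2. If it is two-sided, do one of the following:
   - restate power as about 70% for a mean difference of 1.0 HbA1c point or 3.9 kg, without baseline adjustment; or
   - state, as an assumption, the baseline-to-follow-up correlation (about 0.44 or more by the normal approximation) under which the adjusted analysis reaches 80%.
3. If it is one-sided, say so; the stated 17 centres and 80% then follow from the inputs by the normal approximation.
4. In the abstract, limit the power claim to the HbA1c and weight differences that were calculated, and remove it for self-care activities.

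The cost is a few sentences and, on the two-sided unadjusted reading, a less favourable stated power. Recruitment, data collection and the planned models are unaffected. The Timeline section says that analysis is under way, so the sidedness should be declared before the results are interpreted.

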### Sample selection process

Community health centres that agreed to participate were randomly allocated by computer generated random numbers to either control or intervention groups. All type 2 diabetic patients attending the selected health centre on the recruitment days were invited to participate in the study. Recruitment days were when the health centre had a diabetic club. Centres were visited weekly until the sample of 40 patients per health centre was obtained. Altogether 720 patients were recruited in the intervention arm and 850 in the control arm giving a total of 1570.

### Inclusion and exclusion criteria

Inclusion: All type 2 diabetic patients who gave consent, regardless of the type of medication (oral and/or insulin) or time since diagnosis.

Exclusion: Type 1 diabetic patients, those who refused consent, those who were judged by the clinical nurse practitioner or medical officer as unable to participate in the intervention (for example due to acute illness, mental illness, dementia or another justifiable reason).

